#### Sample size and analysis

Work package 3 is designed to provide two estimates relating to recruitment interventions: (1) the effectiveness of recruitment interventions in the context of a single host trial, and (2) a measure of the variability in effectiveness across multiple host trials.

A large number of trials in primary care and community settings recruit patients with existing health conditions from registers in primary care. For the purposes of the power calculation, we assume that the primary outcome is the proportion of potentially eligible patients who agree to participate following such an invitation. Therefore, the denominator will be the number of patients who are initially invited following screening. It should be noted that this is a larger number than that required for power for an analysis of the primary outcomes within individual trials. For example, a trial which is seeking to recruit 300 patients may need to approach approximately 600 to 1,500, depending on the overall uptake rate. It is the latter, higher figure which is of relevance for the power analysis of START in these contexts.

To provide a conservative sample size estimation, we assume a base response rate of 50% to invitations (although rates in many studies will be significantly lower). We define a significant improvement in recruitment rate as an increase in response of 10%. If individual patients are randomized (for example, to a conventional or optimized participant information sheet), 400 patients per arm would be required to provide 80% power to detect a 10% difference (alpha 0.05). We will plan to restrict START to trials that involve at least this level of recruitment, although we will not exclude studies where interventions can be introduced after recruitment has begun, or where recruitment continues beyond the end of the START study.

It is anticipated that some trials will prefer to use cluster allocation of the START recruitment interventions, to ease the logistical burden on the trial and to ensure the quality of the randomization procedure. We will seek where possible to ensure that the minimum sample size is appropriately inflated in these studies to take into account the cluster allocation, assuming an interclass correlation of 0.02 in line with recent estimates from community studies [43, 44].

To assess effectiveness of recruitment interventions in the context of a single host trial, we will seek to analyze all outcomes of relevance to recruitment, according to the framework developed in work package 1. It is likely that the core analysis will involve dichotomous outcomes (for example randomized or not-randomized) assessed using logistic regression, and controlling for baseline demographic factors. A generic analysis plan is available from our statistician (VM). Where possible, we will work with trials to include additional outcome measures, including patient self-reported outcomes such as satisfaction with information, understanding of the trial, and anxiety. Although recording of data on retention of randomized participants is unlikely to be possible during the timeline of the START study, we will encourage investigators to collect and report data.

In terms of variability across host trials, we will explore this in a meta-analytic framework. The proportions of invited patients recruited into each trial will be entered into a meta-analysis, and the heterogeneity of the intervention effect across trials will be assessed using the I^2^ statistic. If significant heterogeneity is demonstrated, we will explore differences between trials that might explain that variation. The power of any such analyses will be limited because of the small number of trials, but we will explore this issue qualitatively using data collected on the trial, the patient population, and the context of the study. Analyses will be guided by a pre-specified analytic plan. All trial data collected on recruitment and retention facilitated by START will be disseminated in accordance with the MRC START publication strategy during the START funding timeline. Subsequently, data will be captured and reported by the existing Cochrane reviews to ensure their availability outside the START funding and timeline [11, 45].

MRC START has received full ethical approval (Research Ethics Committee: REC Reference: 11/YH/0271) from the National Research Ethics Service (NRES) Committee Yorkshire and the Humber - South Yorkshire, and an MRC START Multimedia Substantial Amendment covering the generic content in the multimedia intervention (REC reference: 11/YH/0271 substantial amendment 2, 31 October 2013). NRES approval will be obtained for each embedded study, via a substantial amendment to the host trial REC.

Patients do not have the opportunity to give informed consent to enter into the embedded recruitment studies. This has been approved by NRES Committee Yorkshire and the Humber - South Yorkshire (REC reference: 11/YH/0271) on the basis that the embedded studies are not withholding information, but are just changing the way it is presented. Each embedded study (standard naming format: ‘MRC START in [insert host trial name]’) will be registered by the host study as a sub-study on the relevant trial registration database.

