### Work package 3: implementation and analysis

#### Trial recruitment

Our long-term aim is to embed the concept of embedding recruitment studies into the funding and startup process of trials in all healthcare settings, and in publicly and commercially funded trials, in order to ensure that delivery of embedded recruitment studies is a routine part of the delivery of trials in the United Kingdom and elsewhere. In the START program, we will work with major funders, clinical trials units, and the research network infrastructure in the United Kingdom to identify and recruit host trials for embedded studies of the recruitment interventions developed in work package 2.

We plan to recruit six trials for each intervention developed in work package 2 (12 in total). Inclusion criteria for the trial are as follows: trials must be at a stage in their delivery where adoption of the embedded recruitment intervention is feasible (for example, about to apply for research ethics approval, early in the recruitment process, or struggling to recruit); trials must be recruiting from primary care or community settings and involving recruitment procedures amenable to the interventions from work package 2; trials must be approaching at least 800 potential research participants; and there must be agreement in principle to take part in START, to randomize using appropriate procedures, to ensure concealment of allocation, deliver the interventions according to a protocol, and share anonymized data on recruitment with the START team as part of an ongoing collaboration.

The aim will be to recruit a sample of host trials (see ‘Sample Size’ below) that all approach patients using broadly comparable recruitment procedures (such as approaching patients from an existing disease register) but do so in relation to different clinical and health service areas and in different contexts. We do not expect all trials demonstrating an interest to be able to participate in START. We will record the process of negotiation and reasons for participation or non-participation to allow us to understand barriers and facilitators to the recruitment of host trials. We will undertake qualitative interviews with principal investigators and other relevant staff (such as trial managers) of host trials after completion of the embedded trial.

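### Variability of effect across host trials is one of two promised estimates, but I-squared does not measure it and a significance trigger with six trials will often miss moderate variation

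*Protocol article*

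**What the plan says.** All references are to the protocol article, work package 3.

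- **Target.** The section on sample size and analysis sets two estimates. One is effectiveness within a single host trial. The other is "a measure of the variability in effectiveness across multiple host trials".
- **Statistic.** Recruited proportions from each trial go into a meta-analysis, and "the heterogeneity of the intervention effect across trials will be assessed using the I^2^ statistic". No between-trial SD, confidence interval or prediction interval is mentioned.
- **Trigger.** "If significant heterogeneity is demonstrated, we will explore differences between trials that might explain that variation". Neither a test level nor an I-squared threshold is attached to the word significant.
- **Caveat.** The next sentence reads: "The power of any such analyses will be limited because of the small number of trials, but we will explore this issue qualitatively".
- **Number of trials.** Under trial recruitment: "We plan to recruit six trials for each intervention developed in work package 2".
- **Further plan.** "Analyses will be guided by a pre-specified analytic plan". That plan is not shown.

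The sample-size calculation covers the single-trial estimate only: 400 per arm for a 10-point gain on a 50% base rate. No power or precision is given for the second estimate.

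**The concern.** Variability of effect is one of only two quantities that work package 3 is designed to estimate, so the statistic attached to it should be on the scale of the effect. I-squared is the proportion of the observed variation between trials that is not sampling error. If the true spread stays the same and the host trials get larger, I-squared rises. If base rates fall, so that each log odds ratio is less precise, it falls. START expects hosts to differ on both counts: the article says many trials will have base rates well below 50%, and the section on preliminary results says smaller and secondary-care trials were later admitted.

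The trigger adds to this. A significance test on six trials has limited ability to detect moderate variation, and it decides whether differences between trials are looked into. What is at stake is practical. An investigator considering one of these interventions wants to know what range of effect to expect in a new trial. The named statistic cannot say, and the follow-up may not start when the spread is large enough to matter.

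**Working it through.** **Step 1. Reproduce the stated figure.** For 50% versus 60%, two-sided 5% and 80% power (sidedness assumed), the usual formula gives 388 per arm, or 408 with continuity correction. With 400 per arm the power is 81.3%. The stated 400 is sound for a single trial.

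**Step 2. Does I-squared track the spread?** Take I² = τ²/(τ² + v), where v = 1/(n·p₁q₁) + 1/(n·p₂q₂) is the variance of a log odds ratio. Hold τ at 0.2 (assumed), so τ² = 0.04, with a mean odds ratio of 1.5 (which takes 50% to 60%).

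| Base rate | n per arm | v | I² |
|---|---|---|---|
| 5% (p₂ = 7.3%) | 400 | 0.0526 + 0.0369 = 0.0895 | 0.04/0.1295 = 31% |
| 50% (p₂ = 60%) | 400 | 0.0100 + 0.0104 = 0.0204 | 0.04/0.0604 = 66% |
| 50% (p₂ = 60%) | 2,000 | 0.00408 | 0.04/0.0441 = 91% |

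The true spread is identical in all three rows. In percentage points the same happens: with τ = 3 points at a 50% base rate, I² is 0.0009/(0.0009 + 0.49/200) = 27% at 200 per arm and 0.0009/(0.0009 + 0.49/2,000) = 79% at 2,000 per arm.

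**Step 3. Power of the trigger.** Inputs: six trials (5 degrees of freedom), 400 per arm, 50% versus 60%. The article gives no test, level or τ, so Cochran's Q at 5% and a range of τ are assumptions, as are equal trial sizes and normally distributed true effects. Within-trial variance is (0.25 + 0.24)/400 = 0.001225, a standard error of 3.5 points. Then Q/(1 + τ²/v) follows χ² with 5 df, and power is P(χ²₅ > 11.07/(1 + τ²/v)). For τ = 3 points: 1 + 9/12.25 = 1.735, 11.07/1.735 = 6.38, power 27%.

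| τ (points) | Power at 5% | Power at 10% |
|---|---|---|
| 2 | 14% | 22% |
| 3 | 27% | 38% |
| 4 | 44% | 55% |
| 5 | 60% | 69% |
| 8 | 88% | 92% |

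Simulation (20,000 meta-analyses per row) agrees to within about one percentage point. Power at 5% passes one half at τ of about 4.3 points and reaches 80% at about 6.8. On the log-odds-ratio scale with τ = 0.2 and 400 per arm, simulated power is 59% at a 50% base rate, 55% at 30% and 26% at 10%.

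**Step 4. What an observed I-squared leaves open.** With six trials, I² must exceed (11.07 − 5)/11.07 = 55% to reach p < 0.05. An observed I² of 50% corresponds to Q = 10, p = 0.075. Inverting the Step 3 distribution gives a 95% interval for τ from 0 to √[(10/0.831 − 1) × 12.25] = 11.6 points. An observed I² of 0% with Q = 5 still allows τ up to 7.8 points.

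**Step 5. What a prediction interval would show.** Take a mean effect of 10 points and τ = 3. The expected 95% interval for a new trial is 10 ± 2.776 × √(9 + (9 + 12.25)/6) = 10 ± 9.8, or about 0.2 to 19.8 points. With τ = 5 it is about −5.5 to 25.5. A spread that the trigger would miss roughly three times in four (τ = 3) is thus consistent with a new trial seeing almost nothing or nearly twice the target gain.

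**The case against.** The article is more careful than the trigger sentence suggests on its own. It concedes limited power in the next sentence and promises a qualitative look at the issue. The section on trial recruitment separately plans interviews with host-trial investigators and staff, with no heterogeneity condition. It also points to a pre-specified plan that may well name the between-trial SD and a prediction interval, and a journal article need not print such detail. All of this stands. It narrows the point to what the article does print: I-squared as the measure, and significance as the trigger. Qualitative exploration, whether or not it is gated (the text is unclear), yields no estimate of spread.

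Several stronger readings are tempting, but the article does not support them:

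- **That the test would usually miss variation.** This depends on a τ the article never states. At 400 per arm and a 50% base rate, it holds only below about 4.3 points; at 5 points or more the test detects more often than it misses.
- **That pooling is on the risk-difference scale**, so that differing base rates alone create heterogeneity. The article enters proportions but names no effect scale, and odds ratios can be computed from those same proportions.
- **That the pooled interval will be too narrow.** No interval method is stated.
- **That a non-significant test will be taken as proof of a uniform effect.** Nothing says so, and the caveat about power points the other way.

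**Conclusion.** The point holds in a limited form. The article assigns its second target estimate to a statistic that does not measure it: the same true spread gives an I-squared anywhere from about 31% to 91% over plausible base rates and trial sizes. That part needs only an assumed τ for illustration and would hold for any non-zero τ.

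The trigger has no stated level and will often miss moderate variation: 27% power at a between-trial SD of 3 points, 44% at 4, 60% at 5. These figures rest on a 5% Q test, six equal trials of 400 per arm, a 50% base rate and assumed SDs. Smaller hosts lower the power; at an assumed 200 per arm, the SD needed for 50% power rises from about 4.3 to about 6.15 points (a factor of √2). Base rates below 50% lower it for a given SD in log odds, although not for a given SD in percentage points.

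This does not invalidate the programme or the single-trial sample size. It also cannot be concluded that the programme will produce no estimate of spread, because the analysis plan is not shown. The text as printed should be corrected because the correction is nearly free and concerns a headline aim.

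**What to change.** For each intervention separately:

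1. Run a random-effects meta-analysis of the log odds ratios, so that the scale matches the within-trial logistic models.
2. Name the between-trial SD (τ) with its confidence interval, and a 95% prediction interval for the effect in a new host trial, as the measure of variability.
3. Keep I-squared as a descriptive figure only.
4. Make the exploration of differences between trials, which will be largely qualitative, unconditional on any significance test.

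The cost is a few lines of text and no extra data. The downside is that with six trials the intervals will be wide, as Steps 4 and 5 of the working show; that width is a fair statement of what six trials can tell. If the unseen analytic plan already specifies this, the only change needed is to bring the article's wording into line with it.

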### Preliminary results

To date, we have completed two rounds of recruitment to START with a third in progress. The recruitment process was designed to test interest in START and explore the feasibility of START becoming self-sustaining. For the first round, trials eligible for START were identified from the Health Technology Assessment (HTA) Programme and Primary Care Research Network (PCRN) databases and sent a START project flyer with a covering letter from either HTA or PCRN encouraging their participation in the START program.

For the second round this procedure was repeated and followed up by the START project team who attempted to contact principal investigators up to three times by phone and a further time by follow-up email. For the final rounds of recruitment we are using project flyers, invitation letters, and intensive phone or email follow-up to establish a more comprehensive picture of the barriers or reasons for non-participation.Figure 4 shows the first round of recruitment to the START project. A total of 60 out of 71 potential trials expressing an interest in START were excluded, primarily due to incompatible recruitment methods or aspects of the host trial design, indicating considerable scope for the development of other recruitment interventions. Of the 11 potential trials identified in the first round of recruitment, 4 became hosts to the PIS intervention, and 7 were subsequently lost due to delays in the development of the multimedia intervention. The second and third recruitment rounds are ongoing, with 10 of the 12 trials recruited to date.

**Figure 4 Fig4:**
[figure not shown]
**Round 1 recruitment outcomes.**

There have been some deviations from the protocol in light of challenges encountered during the work. The initial plan was to recruit trials in primary care or community settings and those approaching 800 potential participants. As the project progressed, these criteria were relaxed to include secondary care and smaller trials that were keen to participate and had recruitment procedures amenable to the START interventions. In one trial the existing PIS was of such high quality that, in the opinion of experts within the START team, the PIS development process being evaluated in START would provide few benefits and the trial was excluded from START.

## Discussion

In the short term, the START program is designed to conduct 12 embedded trials of 2 recruitment interventions, in order to provide a robust assessment of the effects of these interventions across a range of trial settings.

The program is also designed to develop capacity for further adoption of the embedded trial methodology, through development of processes (such as those required to gain consent from ethical and other governance committees), resources (such as reporting guidelines and standardized agreements between researchers from host and embedded trials), and knowledge (for example, concerning core barriers to the delivery of embedded trials, and the optimal methods to encourage adoption).

Initial findings show some difficulty engaging with the wider trial community. Of the trials approached in the first round of recruitment, 70% did not respond, although this may reflect the primary care and community focus evident in the START promotional material. Of those trials expressing an interest, the majority were ineligible. Some reasons for the exclusion of potential host trials (such as timetable issues, n = 25 in total) are limitations of the timeline for this research and would not in general be obstacles to testing recruitment interventions by embedded trial methodology. The fact that over a third of potential host trials were excluded due to recruitment method or other trial design issues (n = 26) highlights the need to develop a broader range of recruitment interventions suitable to varying trial recruitment methods. Further adoption and implementation of the START model is likely to be dependent on the ongoing development of tools and interventions that can be tested using the embedded trials approach, including interventions for professionals [11, 46]. However, as noted earlier, this may lead to additional logistical challenges in implementing embedded recruitment studies which may not be fully explored in the current START protocol, with its focus on lower complexity, patient-level interventions. The development of appropriate incentives to encourage adoption of these methods by busy trial teams is also likely to be important. The more intensive follow-up work on barriers to participation, conducted in the second and third recruitment rounds, will inform development in this area.

The START program will in turn contribute to other developing resources around trials methodology, such as Studies Within A Trial (SWAT [47]) and Trial Forge [48], to meet the longer term aim of making the delivery of embedded recruitment trials routine, and to make a substantive contribution to the development of a science of recruitment.

## Trial status

Recruitment began in March, 2012. The second and third recruitment rounds are ongoing, with 10 of the 12 trials recruited to date.

## Abbreviations

HTA: Health technology and assessment
MRC: Medical Research Council
NRES: National Research Ethics Service
PCRN: Primary Care Research Network
PIS(s): Participant information sheet(s)
PRIMER group: Primary Care Research in Manchester Engagement Resource
REC: Research Ethics Committee
START: Systematic Techniques for Assisting Recruitment to Trials.
